#### Study cohort

We will select a study cohort from the CPRD Aurum to investigate objectives 1–3. We will identify and extract the records in the primary care and HES dataset for all patients with a diagnosis of SMI (hereafter *exposed*) and who are eligible for data linkage. Diagnostic Read codes, which are the standard clinical codes used in UK general practice, will be used to identify an SMI diagnosis. We will also use codes according to the International Classification of Diseases version 10 (ICD-10) from the HES data. The date of the first SMI Read code will be used as the index date, which is the earliest date that an exposed patient may enter the study. From the study cohort, a subcohort of patients will be selected to investigate objective 4. To enter the subcohort, the exposed patient needs a recorded BMI ≥25 kg/m^2^ at any time after the index date. All information will be extracted for the period 01 January 1998 to 31 October 2020—the earliest and latest dates respectively that data are available.

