#### Duration of follow-up

Patients will be followed up in the database from their index date until the earliest of the following: date of death; date of outcome of interest; date of leaving the participating practice; date of the latest download of data; or the end of the study follow-up period (ie, up to 22 years).

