### Exposures

For all analyses, the exposure of interest is SMI. We will extract information on the study cohort up to censoring. Extracted information includes the diagnosis date and type, which will be grouped according to the two major SMI subgroups as classified by the ICD-10: F20-29 non-affective psychotic disorder (ie, schizophrenia, schizotypal and delusional disorders, psychosis not otherwise specified) and F30-39 affective psychotic disorder (ie, bipolar, manic, schizoaffective disorders, major depressive disorder with psychosis). Patients may have Read codes in the primary care data relating to both non-affective and affective psychotic disorders. These will be classified using the most recent Read code because we will assume that the latest diagnosis is the correct one. For example, it is common for diagnoses to be clarified over time from first episode psychosis to schizophrenia. Based on similar studies, instances where there are Read codes relating to both diagnoses at the same date will be coded under non-affective psychotic disorder.^25^ Data on individual prescriptions for psychotropic medication will be extracted from the primary care data from index date until censored.

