### Statistical analysis

Analyses will be conducted in Stata using an estimation approach. We do not intend to impute missing data. The entry date into the analysis is the index date. The outcome date is the earliest of: (1) the date of death or (2) date of diagnosis of the outcome of interest. For objectives 1 and 2, we will use all repeated measures and run separate models for each analyses. For objective 3, we will use the first recorded diagnosis of the outcome of interest rather than recurrent events. Patients who do not have the outcome of interest will be censored at the earliest of: (1) date of death, (2) date of leaving the practice, (3) date of the latest download of data or (4) the study end date.

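### SMI type is set by the latest code during follow-up, so any type-specific CVD or mortality estimate would contain immortal time; the overall SMI versus no-SMI estimates are not affected

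*Protocol article*

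**What the plan says.** Time zero is defined under Study cohort: "The date of the first SMI Read code will be used as the index date". Duration of follow-up and Statistical analysis agree with it: "Patients will be followed up in the database from their index date until the earliest of the following" (death, outcome, leaving the practice, last download or study end), and "The entry date into the analysis is the index date".

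Exposures fixes the type of illness differently. Diagnosis date and type are collected over follow-up ("We will extract information on the study cohort up to censoring"), and types are combined into F20-29 non-affective and F30-39 affective disorder ("which will be grouped according to the two major SMI subgroups as classified by the ICD-10"). It expects overlap: "Patients may have Read codes in the primary care data relating to both non-affective and affective psychotic disorders". For these patients the rule is: "These will be classified using the most recent Read code because we will assume that the latest diagnosis is the correct one". The reason given is that "it is common for diagnoses to be clarified over time from first episode psychosis to schizophrenia". Codes of both types on the same date go to non-affective.

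Primary analyses describes no time-varying type and no split of person-time at a change of code. Sensitivity and secondary analyses does not vary the rule.

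**The concern.** The start of follow-up and the assignment of type use different dates. The index date is the first SMI Read code, so no SMI Read code precedes it, and same-day conflicts have their own tie rule. Whenever the latest-code rule moves a patient across groups, it therefore does so with a code recorded after time zero.

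Take a patient first coded non-affective and recoded affective in year 4. In the CVD analysis this patient cannot have had the outcome, died or left before year 4, yet those four years enter the affective denominator. A similar patient with a CVD event in year 1 never reaches the recoding, and both the event and the time stay under non-affective. The receiving group gains event-free time. The group of first codes loses person-time but keeps its early events.

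At stake are CVD and mortality rates by type, whether the two types are compared with each other or each with the unexposed. The mixed models for objectives 1 and 2 have no event-free person-time of this kind. There, type is a baseline label that depends on the future, so early measurements are grouped by what happened later.

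**Working it through.** **The plan's own figure.** The plan gives no figure on this point. Its sample size concerns SMI versus no SMI and is not in dispute. Risks of 3.0% and 3.9% (RR 1.3), four unexposed per exposed, two-sided 5% and 80% power give 3907 exposed, as stated.

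**Inputs**
- From Sample size calculation: CVD rate λ = 0.01 per year; mean follow-up 4.6 years.
- Assumed, because the documents are silent: end-of-follow-up rate constant at 1/4.6 = 0.2174 per year; half of patients first coded in each type; constant yearly switching rates a (non-affective to affective) and b (the reverse), 0 to 10%; at most one switch; codes counted only up to the end of follow-up for the outcome. The true CVD rate is the same in both types, so the true ratio is 1.00.

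**Formulas.** Let κ = 0.01 + 0.2174 = 0.2274. Per patient whose first type has switching rate s:
- ends before switching: events λ/(κ+s); person-years κ/(κ+s)²
- switches first: probability s/(κ+s); events [s/(κ+s)]·λ/κ; person-years [s/(κ+s)]·[1/(κ+s) + 1/κ], of which the part with 1/(κ+s) is event-free by construction.

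The latest-code rule puts both parts of a switcher's time in the later group.

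**Example, a = 5%, b = 0%**
- Non-affective: events 0.01/0.2774 = 0.03605; person-years 0.2274/0.2774² = 2.955; rate 0.01220.
- Affective, first coded so: events 0.01/0.2274 = 0.04398; person-years 4.398.
- Affective, arrivals: probability 0.05/0.2774 = 0.1803; events 0.1803 × 0.04398 = 0.00793; person-years 0.1803 × (3.605 + 4.398) = 1.443.
- Affective total: 0.05190/5.840 = 0.00889.
- Ratio 0.00889/0.01220 = 0.73. Event-free share of affective person-time: 0.1803 × 3.605/5.840 = 11%.
- Against the unexposed, the non-affective rate is 1.22 times and the affective rate 0.89 times its true value.

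**All scenarios.** The simulation used 2,000,000 patients with follow-up capped at 22 years; its noise is about 0.01 to 0.02.

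| a / b per year | Formula | Simulation, latest code | Simulation, time-updated |
|---|---|---|---|
| 0% / 0% | 1.00 | 0.99 | 0.99 |
| 2% / 2% | 1.00 | 0.98 | 0.98 |
| 5% / 5% | 1.00 | 1.01 | 1.01 |
| 2% / 1% | 0.93 | 0.94 | 1.00 |
| 5% / 2% | 0.86 | 0.86 | 1.00 |
| 10% / 5% | 0.88 | 0.88 | 1.00 |
| 5% / 0% | 0.73 | 0.73 | 1.00 |
| 2% / 5% | 1.16 | 1.16 | 1.00 |

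Balance here means equal rates from groups of equal size. With 60% first coded non-affective, equal rates of 5% give 0.89 by the same formulas.

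**Which replacement works if the later diagnosis is the true one?** Equal hazards cannot show the cost of a wrong first code. A second simulation let the eventual diagnosis set the CVD rate. It assumed 60% first coded non-affective, 20% recoded to affective and 10% the reverse, a mean of 2 years to recoding, and 1.3% per year (1% × 1.3).

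| True ratio | Latest code | Index-date code | Time-updated |
|---|---|---|---|
| 1.00 | 0.93 | 1.00 | 1.00 |
| 0.77 | 0.74 | 0.83 | 0.79 |
| 1.30 | 1.18 | 1.20 | 1.26 |

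Time-updated type is closest, or equal closest, in each row. Index-date coding is further off than the latest code when the true ratio is 0.77.

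**The case against.** The strongest reply is that the plan does not run the analysis that would be biased. Exposures names SMI as the exposure for all analyses, and the objectives and the models under Primary analyses set SMI against no SMI. The subgroup examples are age, sex, ethnicity and SES, and type is not a covariate in Table 2. This stands in part. A reader might infer that the main results are biased, or that an affective versus non-affective comparison is prespecified; the article supports neither. But it does define two groups, an assignment rule and a tie-breaker, and any result by type would inherit the rule.

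The second reply is that the latest diagnosis is the more accurate one. That may be so, but patients with early events never get the chance to be corrected, so accuracy then depends on survival. The reply does stand against making index-date coding the main remedy, as the second table shows.

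Three further inferences go too far:
- That the article calls cross-group change common. Its example, first episode psychosis to schizophrenia, appears to stay within F20-29, where psychosis not otherwise specified is listed. For codes of both types it says only that patients may have them.
- That the affective rate must be pushed down. This needs net movement towards affective, and the article gives no direction.
- That weight trajectories contain immortal time. The mechanism there is different, and no size was computed.

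**Conclusion.** The point holds for type-specific CVD and mortality estimates and no further. The rule as written uses information from after time zero and credits event-free time to the later type. The overall SMI versus no-SMI estimates are unaffected.

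Size and direction are unknown. Under assumed switching of 0 to 10% per year, a true ratio of 1.00 becomes roughly 0.73 to 1.16, and it stays near 1.00 when switching is balanced. In the scenarios with switching, about 4% to 18% of a receiving group's person-time is event-free by construction. Against the design RR of 1.3, the larger of these distortions would matter. The figures rest on constant rates, the assumed starting shares, and codes being counted up to the end of follow-up for the outcome. Only the CVD rate and the mean follow-up come from the article.

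For objectives 1 and 2 the rule conditions on the future; that effect has not been quantified. The change should be made before type-specific results are seen.

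**What to change.** State whether estimates by SMI type are planned. For type-specific time-to-event and rate analyses, treat type as time-updated: person-time before the new code stays under the old type, and person-time from the new code onwards goes to the new type. Report type by codes at the index date, and type by the latest code, only as labelled sensitivity analyses. Tabulate how many patients cross groups, in which direction and when, so that the size of the problem can be seen. If trajectories are shown by type for objectives 1 and 2, say that a label taken from later codes conditions on the future.

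The cost is some rewording and a time-split, since diagnosis dates and types are already to be extracted. The drawback is that some early person-time remains under a less specific first diagnosis, which is why time-updating does not fully recover the true ratio in the second table.

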### Outcomes

The primary aim of objective 1 is to assess the impact of an SMI diagnosis on weight change. A pilot search of the database indicated waist circumference was not reliably recorded so we did not include this as a measure of adiposity. The outcome for objective 2 is change in cardio-metabolic risk factors for CVD, which include change in systolic and diastolic blood pressure, change in total cholesterol/high-density lipoprotein ratio, and change in glycaemia indicated by HbA1c or fasting glucose. The outcome for objective 3 is incidence of and mortality from CVD. The objective for 4 is coded weight management advice and referral to weight management services. We will interpret the data based on the associations for all outcomes, as well as consistency and interpretable patterns. The specific outcomes for each objective are outlined in table 1.

**Table 1 T1:** Outcome measures

Objective	Outcome	Measures
Objective 1: Examine the association between SMI and weight change	Weight change	Absolute mean weight change (kg)
		Percentage weight change (kg)
		Change in body mass index (kg/m^2^)
Objective 2: Examine the association between SMI and changes cardio-metabolic risk factors for CVD	Cardio-metabolic risk	Change in fasting blood glucose (FBG)
		Change in haemoglobin A1c (HbA1c)
		Change in mean total-cholesterol
		Change in triglycerides
		Change in low-density lipoprotein (LDL)
		Change in blood pressure (systolic (SBP) and diastolic (DBP))
Objective 3: Total incident and fatal CVD	Incidence of CVD and CVD fatalities	Angina diagnosed by GP
		Acute coronary syndrome
		Coronary heart disease
		Congestive heart failure
		Cardiomyopathy
		Total stroke
		Total fatal CVD events
Objective 4: Weight management advice and service referral	Proportion (%) of exposed and unexposed who are recorded as offered advice, and then offered and actually referred to a weight management service	

CVD, cardiovascular disease; GP, general practitioner; SMI, serious mental illness.

### Confounding

We have identified confounding variables using directed acyclic graphs (DAGs), which aims to theoretically formalise potential confounders, colliders and biasing relationships.^26^ The DAG for each objective is described in online supplemental material S1. The DAG for objective 1 shows one direct path from the exposure (ie, SMI) to the outcome (ie, weight change), and four indirect paths: via health behaviours (ie, alcohol use, smoking and diet), SES status, psychotropic medication, and healthcare access and provision. Diet and physical activity are latent variables in CPRD Aurum because they are unmeasured. There are three confounding paths: via age, sex and ethnicity.^27 28^ Thus, the minimally sufficient adjustment for the total effect of SMI status on weight is to adjust for age, sex, and ethnicity.

10.1136/bmjopen-2021-053427.supp1Supplementary data

Frequency matching will ensure our ability to adjust for confounding variables that include age, sex, and calendar year, and matching on practice will remove practice-specific variables. In addition, we will fully adjust our models by considering several covariates in the relationship between the exposure and outcome (see table 2). All categorical variables will be analysed using the natural reference category as the reference group. Data on individual prescriptions for psychotropic and cardio-metabolic medications will be extracted from the primary care data from index date until censoring. For psychotropic medications, drugs will be classified according to the British National Formulary. For objectives 2 and 3, we will assess the impact of weight gain on change in cardio-metabolic risk factors and incidence of CVD using mediation analysis to allow us to estimate the direct (unmediated) and indirect (mediated) effects of SMI on CVD risk and incidence. To do this, we will fit two regression models: one regressing the outcome on the exposure, adjusting for confounders and another regressing the mediator on the exposure and confounders using the Stata *Med4way* command to estimate mediated effects.^29^ For objective 4, we will assess the presence of confounding by comparing estimates with and without adjustment. We will use Read codes, which have been previously developed by our team, to identify outcome and covariate records.

**Table 2 T2:** Confounders

Confounders and covariates		Measures
Health behaviours	Smoking status	Categorical (0=never; 1=ex-smoker; 2=current smoker (light: 1–9 cigarettes/day; moderate: 10–19 cigarettes/day; heavy: 20+ cigarettes/day)). This is coded in GP records. We will use the most recent recorded value of smoking status at the study start date.
	Alcohol use	Continuous (units per week). This is coded in GP records. We will use the most recent recorded value of alcohol use at the study start date.
Demographics	Socioeconomic status (SES)*	Categorical (quintiles)
	Ethnicity†	Categorical (white; Asian or Asian British; black or black British; other ethnic group, mixed)
	Sex†	Binary (0=male; 1=female)
	Age at study entry, in years	Continuous
Physical and/or medical factors	Baseline weight status (body mass index (BMI))	Categorical (normal weight (BMI 18.5–24.9 kg/m^2^); overweight (25.0–29.9); obese (30.0–34.9); severe obesity (35.0–35.9); morbid obesity (40.0–44.9)
	Psychotropic medication	Categorical (antipsychotics (first-generation and second-generation); antidepressants; mood stabilisers)
	Cardio-metabolic medication	Categorical (blood glucose lowering medications; antihypertensive treatments, statins)
We include the following additional variables for objectives 3 and 4 only		
CVD risk factors	Total cholesterol/HDL ratio	Continuous
	Systolic and diastolic blood pressure	Continuous
	Glycaemia	HbA1c/fasting blood glucose (FBG)

*This variable is grouped according to practice level Index of Multiple Deprivation. This is an indicator of material deprivation based on income; employment; health deprivation and disability; education, skills and training; crime; barriers to housing and services; and living environment. It is categorised as quintiles 1–5 with 1 being the most deprived and 5 being the least deprived.

†This variable is grouped according to recommendations by the UK Office for National Statistics.^33 34^

CVD, cardiovascular disease; GP, general practitioner; HbA1c, haemoglobin A1c; HDL, high-density lipoprotein.

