**Methods and analysis:**

In this retrospective cohort study, we will link general practice records from the UK Clinical Practice Research Datalink Aurum database. We will establish a cohort of patients diagnosed with SMI between 1998 and 2020 who are matched with up to four controls on age, sex, general practice and calendar year. We will use multivariable mixed-effects linear regression models and Cox proportional hazard models with sequential adjustment for potential confounders identified by separate directed acyclic graphs.

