Since the study is descriptive, any association observed would not imply an SMI diagnosis is causative of adverse physical health outcomes. However, we might assume the greater the magnitude of the observed association the less likely it is due to bias and more likely due to a causal process.^32^ Furthermore, diet and physical activity are unmeasured confounders because they are unobserved in CPRD Aurum. Similarly, other unmeasured confounders like poverty may place people with SMI at increased risk of homelessness, which has consequences on healthcare access and provision. We address this potential confounding by linking to patient level IMD as a proxy measure of SES, but acknowledge this may not fully capture deprivation and leaves room for residual confounding. Moreover, information bias may be present since the CPRD Aurum relies on a GP recording of health outcomes. Furthermore, we can only examine primary care prescriptions. Any prescribing solely within secondary care may not be included as this was not historically routinely recorded in GP records. Thus, it is possible we will miss the first prescription(s). Finally, physical health checks are not always performed on random samples of the population, and it is possible that more regular testing is done on people with overweight and obesity. We expect that some patients will have incomplete information recorded. However, by determining what proportion of patients do not have appropriate information recorded, we can evaluate the scale of these problems, and highlight the need for improved recording for continuity of care between healthcare professionals.

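### For objective 1, the fully adjusted model includes variables that the plan's own DAG places on the path from SMI to weight, above all post-index psychotropic medication, so it does not estimate the stated total effect

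*Protocol article*

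**What the plan says.** Under Outcomes, the target of objective 1 is worded causally: "The primary aim of objective 1 is to assess the impact of an SMI diagnosis on weight change".

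Under Confounding, the DAG for objective 1 is described as having one direct path, three confounding paths (age, sex, ethnicity), and "four indirect paths: via health behaviours (ie, alcohol use, smoking and diet), SES status, psychotropic medication, and healthcare access and provision". The section concludes: "Thus, the minimally sufficient adjustment for the total effect of SMI status on weight is to adjust for age, sex, and ethnicity".

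The next paragraph of that section adds: "In addition, we will fully adjust our models by considering several covariates in the relationship between the exposure and outcome (see table 2". Table 2 is titled as confounders, and its first column is headed as confounders and covariates. It lists smoking, alcohol, SES and psychotropic medication alongside age, sex and ethnicity.

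The Abstract promises "sequential adjustment for potential confounders identified by separate directed acyclic graphs". The Discussion states that "diet and physical activity are unmeasured confounders because they are unobserved in CPRD Aurum".

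**The concern.** The same variables are given two causal roles. In the DAG description, smoking, alcohol, SES and psychotropic medication are routes by which SMI acts on weight. In Table 2 they stand with age, sex and ethnicity as things to adjust for, under a title that calls them confounders.

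The two models estimate different quantities. The model with age, sex and ethnicity targets the total effect. A model that also holds pathway variables fixed targets something closer to a direct effect. It may also pick up bias from unmeasured common causes of the pathway variable and weight. Because the added variables are labelled confounders, a reader is likely to take the fuller model as better confounding control. A small SMI coefficient in that model could then be read as little impact of SMI on weight, when it might only mean that much of the impact runs through treatment.

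**Working it through.** No figure in the plan bears on this point; the sample size calculation concerns CVD. The check is to set each variable's place in the objective 1 DAG beside its place in Table 2 and the time at which it is measured.

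| Variable | Role in the DAG description | In Table 2? | When measured |
|---|---|---|---|
| Age, sex, ethnicity | Confounding path | Yes | Age at study entry; sex and ethnicity fixed |
| Psychotropic medication | Indirect path | Yes | Index date to censoring |
| Smoking, alcohol | Indirect path (health behaviours) | Yes | Most recent value at study start, read here as baseline |
| SES | Indirect path | Yes | Practice-level IMD (Table 2 footnote; Data linkage) |
| Diet | Indirect path (health behaviours) | No, unmeasured | Not applicable |
| Healthcare access and provision | Indirect path | No | Not applicable |

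**Psychotropic medication.** It is on an indirect path, in the adjustment table and measured after exposure. Under Primary analyses, the effect on weight change is carried by the SMI-by-time term, and models with medication also contain medication-by-time terms. Any weight trajectory that arises through medication is then credited to medication and leaves the SMI-by-time coefficient.

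**Smoking and alcohol.** These are baseline values. Smoking or drinking that began before SMI cannot be its consequence, so adjusting for them removes less than adjusting for post-index values would. How much less is unknown.

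**SES.** A practice-level score is the same for an exposed patient and controls from the same practice. Adjusting for it changes the SMI contrast very little. Data linkage also assigns IMD to descriptive and secondary analyses.

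**Illustration of the medication path.** All values here are invented, because the documents supply none. Let the direct effect of SMI be *d*, the effect of medication on weight *b*, and the proportions medicated *p*₁ (exposed) and *p*₀ (unexposed), in a linear model without interaction.

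- Total effect = *d* + *b*(*p*₁ − *p*₀).
- Effect after adjusting for medication = *d*.
- Share removed = *b*(*p*₁ − *p*₀) / [*d* + *b*(*p*₁ − *p*₀)].

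With *d* = 1 kg and *b* = 3 kg:

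- At 80% against 15% medicated, the total is 1 + 3 × 0.65 = 2.95 kg and the adjusted effect is 1 kg. The share removed is 1.95/2.95 = 66%. A simulation of 200,000 people gave 2.90 and 0.95 kg.
- At 60% against 10% medicated, the total is 1 + 3 × 0.50 = 2.50 kg and the adjusted effect is 1 kg. The share removed is 1.50/2.50 = 60%. The simulation gave 2.53 and 1.02 kg.

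The share falls to zero if medication has no effect on weight (*b* = 0) or is used equally in both groups. These values show the mechanism and are not an estimate for this study.

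**The case against.** The strongest reply is that nothing is lost. The plan itself states which set identifies the total effect. Sequential adjustment implies that less adjusted estimates will be reported beside the full model, and the wording about models incorporating medication suggests that some models leave it out. The Discussion calls the study descriptive and disclaims causation. Which step is headlined is commonly left to an analysis plan that is not shown here.

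Much of this stands. A reader might infer that the total effect will go unreported; the documents do not support that. Nor is the absence of a named primary step a fault in itself. What remains is a contradiction within one section: variables placed on indirect paths are then tabled as confounders, while the aim is worded as impact and the target as a total effect. A separate analysis plan could name a primary model, but this document would still give those variables two roles. The planned mediation analysis does not resolve it, because it covers weight gain as a mediator for objectives 2 and 3, not the indirect paths of objective 1.

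Three further readings are tempting but unsupported.

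- **The same error distorts the CVD result.** The DAGs for the other objectives are in a supplement that is not shown, so this cannot be judged.
- **Adjusting for deprivation hides an SMI effect.** This does not follow from practice-level IMD with practice-matched controls. The Discussion does speak of patient-level IMD, which is a separate inconsistency; the conclusion here rests on the practice-level definition.
- **The whole smoking excess in SMI is removed.** The Introduction reports a difference in prevalence, and baseline smoking may precede diagnosis.

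Loss of power is not the issue either: the feasibility estimate is 135 870 patients with SMI. The risk is a precise estimate of a different quantity.

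**Conclusion.** The point holds for objective 1. Judged by the plan's own DAG, the fully adjusted model does not estimate the total effect of SMI on weight, because it conditions on variables that the DAG places on indirect paths. Psychotropic medication is the clear case. Smoking and alcohol are a smaller and uncertain one, and practice-level IMD is close to none.

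The size cannot be calculated from the documents. That adjustment would make the estimate smaller, and not merely different, assumes that the removed path acts in the same direction as the rest of the effect. The Introduction's account of drug-related weight gain makes this plausible for medication; the documents do not establish it for every path. The conclusion also assumes that the full adjustment uses the medication data extracted after the index date, as the Confounding section indicates.

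**What to change.** - Name the model adjusted for age, sex and ethnicity plus the matching factors as the primary total-effect estimate for objective 1.
- Label models that add indirect-path variables from Table 2, above all psychotropic medication, as secondary and not a total effect.
- Split Table 2 into confounders and pathway variables.
- Bring the Discussion's wording on diet and physical activity into line with the roles the DAG gives them.
- For objectives 2 to 4, apply the same rule with each objective's own DAG in the supplement.

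The cost is wording only. The models already fit within the planned sequential adjustment, no further data are needed and the sample size is unaffected. One small downside: readers who regard pre-index smoking or alcohol as confounders must look to the secondary model.

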#### Exclusion criteria

Patients will be excluded from the cohort(s) if they: have less than 1 year of active data in their participating practice before the index date; and/or who have a Read code for coronary heart disease, congestive heart failure or cardiomyopathy, and/or stroke before the index date. A flow diagram will present the selection and exclusion (with reasons where possible) of patients in the study.

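### The stated prescription window starts at the index date, so the fully adjusted SMI estimates condition on post-exposure medication and have no measure of use before diagnosis

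*Protocol article*

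**What the plan says.** The prescription window is given twice. Under Exposures: "Data on individual prescriptions for psychotropic medication will be extracted from the primary care data from index date until censored". Under Confounding, now including cardio-metabolic drugs: "Data on individual prescriptions for psychotropic and cardio-metabolic medications will be extracted from the primary care data from index date until censoring".

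The starting point is defined under Study cohort: "The date of the first SMI Read code will be used as the index date". The same section gives a broader general period: "All information will be extracted for the period 01 January 1998 to 31 October 2020".

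Table 2, titled as the list of confounders, includes both medication variables, and the Confounding section says the models will be fully adjusted with reference to that table. In the table, smoking and alcohol take the latest value at study start and BMI is labelled as baseline. The two medication rows name drug classes (for psychotropics, "Categorical (antipsychotics (first-generation and second-generation); antidepressants; mood stabilisers") without a time anchor.

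For objective 1, the Confounding section places psychotropic medication on an indirect path from SMI to weight and gives age, sex and ethnicity as the minimally sufficient adjustment set. The Abstract says adjustment will be sequential.

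**The concern.** A confounder has to be measured before the exposure, or at least not be affected by it. A covariate built from prescriptions issued after an SMI diagnosis is neither. Adjusting for it removes part of the effect that the model is meant to estimate. Where the drug is prescribed in response to the outcome, it also conditions on the outcome's own history. Drug use before diagnosis, which could legitimately be adjusted for, is not captured by the stated window.

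At stake is the meaning of the fully adjusted results for objectives 1 to 3. If the coefficient for SMI on weight, blood pressure, lipids, glycaemia or CVD shrinks after full adjustment, a reader will take the difference as confounding removed. Part of it would be an effect of SMI acting through treatment, or selection on response to the outcome.

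**Working it through.** The plan gives no figure on this point, and the medication window does not enter the sample size calculation. The check is a comparison of the passages.

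1. **Timing.** Set time 0 at the index date, which is the first SMI code. The stated window is time 0 to censoring. A covariate built from it uses only prescriptions issued at or after the start of exposure.

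2. **Time anchors in Table 2.**
   - Smoking status: latest value at study start.
   - Alcohol use: latest value at study start.
   - BMI: baseline.
   - Psychotropic medication: no anchor; stated window is post-index.
   - Cardio-metabolic medication: no anchor; stated window is post-index.

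   Unlike the smoking, alcohol and BMI rows, the two medication rows draw on data that the text places after exposure.

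3. **Objective 1.** In the plan's own DAG the total effect of SMI on weight is the direct path plus four indirect paths, one of which runs through psychotropic medication. Adjusting for post-index psychotropics blocks that path. The adjusted coefficient is then no longer the total effect, and the plan does not give it another name.

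4. **Objective 2.** The outcomes are changes in blood pressure, lipids and glycaemia, using all repeated measures. The covariate is antihypertensives, statins and glucose-lowering drugs. These may be started because those measures rose. Comparing SMI and control patients at equal post-index treatment therefore holds fixed a possible consequence of the outcome. The direction of the resulting bias depends on how testing and treatment differ between the groups, which the article does not quantify.

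5. **Objectives 2 and 3, baseline use.** The exclusion criteria remove prior coronary heart disease, heart failure, cardiomyopathy and stroke. They do not remove treated hypertension, dyslipidaemia or diabetes, so patients already on cardio-metabolic drugs at index remain in the cohort. A prescription shortly after index may continue earlier use, but within the stated window it cannot be told apart from a new start.

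6. **Is a look-back possible?** The exclusion criteria remove patients who "have less than 1 year of active data in their participating practice before the index date". A 12-month pre-index window is therefore already guaranteed by eligibility and is not used for prescriptions.

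7. **What is not affected.** The estimate adjusted for age, sex and ethnicity contains no medication term, so the window cannot bias it.

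**The case against.** The strongest reply has four parts.

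- *The general extraction period covers pre-index time.* It does, so the data may be obtainable. But the narrower window is specific to prescriptions and is stated twice, and a general sentence does not override it. The two at least need reconciling.
- *Medication adjustment is an extra step.* This stands. Adjustment is sequential, the minimal set for objective 1 excludes medication, and the column heading in Table 2 covers covariates as well as confounders. The problem is confined to the fully adjusted models.
- *Post-index prescribing is legitimate for studying medication.* This also stands. The mixed models with medication-by-time terms are a proper use of such data. The mediation analysis described concerns weight gain, however, so it does not explain why drugs appear among the confounders.
- *An analysis plan may supply the definitions.* It may say how medication is coded and whether it is time-updated. It could not build a baseline value from prescriptions that the protocol says start at index.

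Three stronger readings are tempting but not supported:

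- A reader might infer that drugs prescribed after a CVD event enter the model. Duration of follow-up ends at the outcome, so on a plain reading they do not. The Statistical analysis section defines censoring only for others ("Patients who do not have the outcome of interest will be censored at the earliest of"), which is a small gap in wording.
- A reader might infer immortal-time bias in drug comparisons. That needs a fixed ever/never drug variable compared in a CVD model. The article states no such analysis and names SMI as the exposure throughout.
- A reader might infer that psychotropics form one variable with no untreated level. The table cell is condensed, and the text promises natural reference categories, for which untreated is an obvious reading.

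**Conclusion.** The concern holds for the fully adjusted models of objectives 1 to 3. As written, they condition on treatment that follows exposure, and they have no measure of cardio-metabolic drug use before diagnosis. For psychotropics under objective 1 this rests on the plan's own DAG. For cardio-metabolic drugs it rests on two assumptions: that such drugs may be started because the measured risk factor rose, and that prior use is a plausible baseline confounder. The DAGs for the other objectives are in a supplement that is not shown, so the second assumption cannot be checked against them.

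No numerical size can be given, because the article contains no prescribing prevalence or starting rates. The minimally adjusted estimate is sound in this respect, so the matter is one of interpreting the fully adjusted results. It is worth settling before prescriptions are extracted.

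**What to change.** 1. Reconcile the windows under Exposures and Confounding with the general period under Study cohort, by extracting psychotropic and cardio-metabolic prescriptions from 12 months before index. Index dates in 1998 would need prescriptions from 1997, before the stated period opens; say how these patients are handled.
2. In Table 2, define the medication covariates as use by drug class in the 12 months before index, anchored at baseline like smoking, alcohol and BMI.
3. Keep post-index prescribing out of confounder-adjusted models of the SMI effect. Use it only as time-updated medication, in analyses labelled as medication or mediation analyses.
4. State for each reported model whether it targets the total effect of SMI or an effect net of treatment.

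The cost is a wider extraction window and some coding work. Eligibility need not change, since a year of prior data is already required.
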